The participant must complete the same 16 tasks in the same order as stage 1; however, the participant must now use Taskiir to help them answer the question and to find evidence to support their answer. Evidence is collected by the participant selecting text, images, or both from the source documents they read. The time allocated to search for each task is set according to the timing cohort the participant belongs to and will be one of 3, 6, or 9 min. The participant is told of the time allocation at the start of each question and a minute-by-minute countdown timer is always visible to the participant; warnings are given 30 seconds before time-out. At time-out, the screen is blocked, and the participant is taken to the task completion screen to enter their final details. Other methods of communicating the time limit were trialed during development of the system. In the end, the above method was chosen because it provided a balance between (1) making the participant aware of the time allocated for each question, (2) avoiding time anchoring (where the participant incorrectly assumed all questions are allocated the same time as the first question), (3) keeping them updated with the time remaining so they do not run out of time without warning, and (4) not distracting the participant with time information (eg, using a second-by-second countdown timer that diverted too much attention away from the task).

As this is the first such study measuring the impact of time variation, a few time limits covering a wide range are required to generate significant differences in the outcomes. A useful starting point to establish these time limits is the average completion time of 6.1 min per question, reported in the Westbrook study [33]. From the same study, the SD, based on the average completion times for each of the 8 questions, across 2 systems, is 3.1 min. Therefore, time limits are set at the average question answer time (6 min) and approximately 1 SD either side of this (3 and 9 min). These limits should induce time pressures for 84% of questions with a 3-min time limit, 50% of questions with a 6-min time limit, and 16% of questions with a 9-min time limit. From previous studies, realistic answer timeframes for busy clinicians should be below 5 min [3,15,35], so the 3 proposed time limit cohorts will encompass this pragmatic indicator of search time suitability.

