#### Data Capture

Immediately after initial login, participant information is captured as per the table in the Multimedia Appendix 1. Data capture then occurs on both the presearch and postsearch answer screens, as listed in Table 1. All system interactions will also be captured including (1) overall time spent searching for and answering each question; (2) dwell times before first query, on the SERP screen, on the document viewing screen, and on the answer screen; (3) the participant’s search query terms and resulting SERP; (4) documents selected from the SERP; (5) evidence selected by the participant from the documents they are viewing; and (6) relevance ratings by the participant of the documents they view (essential, helpful, duplicate-essential, duplicate-helpful, and not helpful). Multimedia Appendix 3 itemizes the search interaction times and how these relate to the study timings. Although desirable, it is not possible to question the participant regarding the utility of each search system because the user is not made aware of which search system is in use for each task.

Anonymity of the data collected is maintained by (1) identifying users and all of their interactions with a random user identification within the data capture system, (2) having no participant identification information stored in the same system database, and (3) capturing only generic participant information (see Multimedia Appendix 1) that could not be used to identify an individual.

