### Statistical Analyses

To assess the impact of introducing the SML search system on clinical decision quality (RQ-1), each participant’s answer, both presearch and postsearch, will be coded to right (R) or wrong by comparing the participant’s answer with an expert judged assessment (gold answer) of each task. Samples for which (1) no evidence is captured and (2) no relevant documents are marked (either as essential or helpful), by the participant for their postsearch answer, will be discarded, as the value of the search system cannot be confirmed in these cases. Therefore, the decision quality is defined by the correct answer rate (number of right answers/total sample count (N)). A further detailed analysis will be performed of the collected evidence to identify tasks where the literature may contradict the gold answers. Where this occurs, the task answers will be reviewed by experts and overall correct rates adjusted.

To assess the significance of any change in the proportion of right or wrong answers, the McNemar test will be employed because it is a nonparametric test suited to a binary result, with samples taken at 2 points in time. Nonparametric is a better model to assume, given that the data distribution is unlikely to be regular because of the different medical groupings of participants. The sign test, which is also a nonparametric test, will be used to identify any significant changes to the correct rate. To assess any differences between the participant groups (nurses, doctors, and students), a Chi-square analysis will be performed. The participant’s confidence in their answers will be assessed presearch and postsearch to identify any significant changes relating to search intervention, also using chi-square analysis.

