To assess the impact of time constraints on clinical decision quality (RQ-2), the analyses above will be repeated with a breakdown by time constraint category, that is, 3, 6 and 9 min. In addition, an analysis of time-outs by constraint category will be conducted to assess the impact of time constraints on task completion. Time-outs are defined as samples where at the postsearch answer stage (1) the task timer reaches the constraint duration and (2) the participant provides no evidence to support their answer. It is assumed that in a time-out scenario, the participant was unable to complete the task. Significant differences by time-constraint category will be analyzed using the chi-square analysis. An analysis of variance (ANOVA) will be performed across confidence, difficulty, participant-perceived time impact assessments (impact of time on answer, evidence capture, and stress), and search behaviors, such as SERP dwell time, number of queries issued, number of documents opened, and the quantity of evidence items selected. To gain an understanding of the impact of providing a time constraint on the decision-making process, both the average time to search and the average proportion of available search time used will be evaluated and compared for the different task-timing samples. Tombros et al [67] used this proportional figure as a further gauge of participant stress and it can be compared with the reported stress by the participants.

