To assess the impact of search engine performance on clinical decision quality (RQ-3), a similar set of analyses will be performed as that for RQ-1, except broken down by search system (state-of-the-art and BM25). In addition, the same ANOVA methods employed for time-constraint categories in RQ-2 analysis will be performed. In addition, an ANOVA will be performed across system categories and system time constraints to identify cases where system performance effects may matter most. The impact of search engine performance on clinical decision time (RQ-3) will also be assessed by evaluating the postsearch task completion times for those tasks that were completed (ie, relevant documents and/or evidence identified). This is measured in 2 ways: (1) search time only and (2) search time plus time spent filling in the answer form. Differences in search times between the systems will be assessed using the chi-square analysis. Finally, a participant-derived performance assessment of the 2 systems can be constructed by building a graded query relevance (QREL) listing (standard format for representing relevance assessments in IR), by query, based on all participants’ relevance ratings. Using this QREL, a recomparison of the 2 systems can be evaluated and compared using the formal TREC evaluation results to provide better insight into any changes observed (or not) in the clinical decision and timing results for the 2 systems.

There are a number of potentially confounding factors within the experimentation. A covariant analysis (repeated measure ANOVA) will be performed on the task number, task at total duration point (for fatigue), and time transitions (eg, 3-min task to 6-min task and 3-min task to 9-min task).

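### The RQ-2 time-out and RQ-3 completed definitions overlap, and timer-stopped tasks enter the RQ-3 time comparison at the cap as if it were a finishing time

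*Protocol article*

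**What the plan says.** The stage 2 procedure (Procedures, In Stage 2) uses time-out for expiry of the timer alone: "At time-out, the screen is blocked, and the participant is taken to the task completion screen to enter their final details". The participant can still give an answer at that point.

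Statistical Analyses then sets three rules that bear on the same tasks:

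- **Discard rule (RQ-1, carried into RQ-2 and RQ-3).** A sample without captured evidence is dropped if it also meets a second condition: "no relevant documents are marked (either as essential or helpful), by the participant for their postsearch answer, will be discarded".
- **Time-out (RQ-2).** The conditions are that "the task timer reaches the constraint duration and (2) the participant provides no evidence to support their answer". The meaning attached to it is: "It is assumed that in a time-out scenario, the participant was unable to complete the task".
- **Completed (RQ-3).** Decision time is assessed from "postsearch task completion times for those tasks that were completed (ie, relevant documents and/or evidence identified". It is measured as search time alone and as search time plus time on the answer form. The timer plays no part in this definition.

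Data Capture lists selected evidence and, as a separate item, "relevance ratings by the participant of the documents they view (essential, helpful, duplicate-essential, duplicate-helpful, and not helpful". A document rated relevant with no evidence selected is therefore a state the system can record.

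**The concern.** Time-out turns on evidence alone, while completed turns on evidence or a marked document. A task can satisfy both, so the plan can describe one task as not completed in one analysis and completed in the next.

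The second issue follows from the missing timer condition in RQ-3. RQ3 under Study Aims asks whether a better search system gives faster decisions. When the timer stops a task, its recorded search time is the limit. If both systems run to the limit on a task, their search times are equal whatever the true difference. Such tasks should not be rare: the protocol expects time pressure on "84% of questions with a 3-min time limit, 50% of questions with a 6-min time limit, and 16% of questions with a 9-min time limit".

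**Working it through.** **The plan's own figure.** In Stage 2 gives a mean completion time of 6.1 min and an SD of 3.1 min, and sets limits at about the mean and 1 SD either side. Normal upper tails at −1, 0 and +1 SD are 84.1%, 50.0% and 15.9%, which reproduces the stated 84%, 50% and 16%. With the unrounded mean and SD, P(time > limit) = 1 − Φ((limit − 6.1)/3.1):

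- 3 min: z = −1.00, 84.1%
- 6 min: z = −0.03, 51.3%
- 9 min: z = 0.94, 17.5%

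**The definitions side by side.** There are eight combinations of timer reached, evidence saved and document marked relevant. I read relevant in RQ-3 as in the discard rule.

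| Timer reached | Evidence | Relevant document | Time-out (RQ-2) | Completed (RQ-3) | Discarded |
|---|---|---|---|---|---|
| no | no | no | no | no | yes |
| no | no | yes | no | yes | no |
| no | yes | no | no | yes | no |
| no | yes | yes | no | yes | no |
| yes | no | no | yes | no | yes |
| yes | no | yes | **yes** | **yes** | no |
| yes | yes | no | no | yes | no |
| yes | yes | yes | no | yes | no |

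Three things follow.

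1. Exactly one combination is contradictory: timer reached, no evidence, relevant document marked.
2. Only two combinations are RQ-2 time-outs, and one of them is removed by the discard rule. The text does not say whether discarded samples return for the time-out analysis. If they stay out, every remaining time-out is also a completed task in RQ-3. If they return, the overlap is partial.
3. In the last three rows the task is completed for RQ-3 and its search time equals the limit. No handling of such values is stated.

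**Illustration of size.** The documents give no counts, so this rests on assumptions: individual task times are Normal(6.1, 3.1), although the source SD is of average times per question; every task longer than the limit is stopped by the timer; every task ended earlier has evidence or a relevant document. Let p be the share reaching the limit, s the share of those with evidence saved, and d the share of the remainder with a document marked relevant.

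- RQ-2 time-outs = p(1 − s)
- Both time-out and completed = p(1 − s)d
- Completed = (1 − p) + ps + p(1 − s)d
- Share of completed times at the cap = [ps + p(1 − s)d] / completed

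At 6 min with s = d = 0.5: time-outs 0.513 × 0.5 = 25.6%; overlap 0.256 × 0.5 = 12.8%; completed 0.487 + 0.256 + 0.128 = 87.2%; at the cap (0.256 + 0.128)/0.872 = 44%.

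| Limit | s | d | RQ-2 time-outs | Time-out and completed | Completed times at cap |
|---|---|---|---|---|---|
| 3 min | 0.5 | 0.5 | 42.1% | 21.0% | 79.9% |
| 6 min | 0 | 0 | 51.3% | 0% | 0% |
| 6 min | 0.5 | 0 | 25.6% | 0% | 34.5% |
| 6 min | 0.5 | 0.5 | 25.6% | 12.8% | 44.1% |
| 6 min | 0 | 1 | 51.3% | 51.3% | 51.3% |
| 9 min | 0.5 | 0.5 | 8.7% | 4.4% | 13.7% |

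At 6 min the overlap can be anything from 0% to 51.3%. The third row shows that capped times arise even where the overlap is zero.

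**The case against.** The strongest defence is that the RQ-2 definition is coherent for its purpose. Stage 2 makes finding evidence part of the task, and the time-out analysis is meant to show how limits affect completion. Timer reached with nothing saved is a reasonable composite for failing to complete because of time. Whether the limit was felt is covered separately by the proportion of available time used and by the Table 1 ratings of time adequacy and stress. Reach is also limited: the correct-answer rate and its tests depend on the discard rule, not on either disputed definition.

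All of that stands, and it rules out a stronger reading. A reader might infer that a participant cut off with one saved snippet is misclassified, so that time-out rates are wrong under the plan's own terms. The documents do not support this. The RQ-2 and RQ-3 definitions agree that such a task is completed. The In Stage 2 use of the word describes screen behaviour, and Statistical Analyses gives the analytic definition; the two senses are loose terminology.

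Nor can a distortion between limits be shown. It would need the share saving evidence to differ by limit, for which there is no source. With an equal share at all limits, and taking the stated percentages as timer stops, the 3 versus 9 min ratio stays at 84/16 = 5.25. Those percentages are in any case expected time pressure, not rates of reaching the limit. A difference by search system is equally unshown.

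The defence does not answer the one contradictory combination or the use of capped search times as completion times.

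**Conclusion.** The point holds in a limited form. The time-out and completed definitions conflict for a task stopped at the limit with a relevant document marked and no evidence saved. Separately, all timer-stopped tasks counted as completed bring a capped search time into the RQ-3 comparison, which can mask a difference in speed.

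The contradiction is in the text and needs no assumed numbers; it requires only that ratings and evidence be recorded separately, as Data Capture says. Its effect on results cannot be sized, and it vanishes if no such documents are marked. The capping problem requires only that some tasks reach the limit with evidence or a marked document. What is affected is the supplementary RQ-2 time-out count and the RQ-3 time comparison.

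**What to change.** 1. Reconcile In Stage 2 and the three rules in Statistical Analyses, so that one rule decides whether a task at the limit with a marked document but no evidence is completed. Apply it in both RQ-2 and RQ-3.
2. State whether samples removed by the discard rule count in the time-out analysis.
3. Report timer expiry by time limit and search system as its own outcome, cross-tabulated with no evidence and no relevant document, alongside the existing composite.
4. In RQ-3, analyse search times with timer expiry as the censoring indicator, for example a time-to-event comparison by system stratified by time limit. Do not treat capped values as completion times.

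Completed should not be redefined as ending before the limit. That would count a participant who gives up early with nothing found, exclude one who used the full time and saved good evidence, and leave no censored times among completed tasks.

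The cost is some rewording and slightly more analysis. No new data are needed: the RQ-2 definition already requires the timer event, and Data Capture already records time per question.

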5	Perceived impact of time constraint on decision: relationship with decision quality and confidence	How would you rate the time you had available to collect evidence? (1=not nearly enough time, 2=nearly enough time, 3=just enough time, 4=more than enough time, and 5=much more than enough time)	N/A	Yes
6	Perceived impact of time constraint on participant’s stress level: relationship with decision quality and confidence	How much stress did you feel due to time pressure? (1=none, 2=a little, 3=a moderate amount, 4=a lot, and 5=more than a lot)	N/A	Yes

**Table 2 table2:** Task specifications including the full task scenario supplied to the participant as well as the relevant reference from the corpus that supports the answer.

Question	Source
Cytobrush Pap Smear: Is the Cytobrush superior to a spatula for obtaining cells for Pap smears, in terms of technical quality (eg, percentage of interpretable smears)? [18]	[38,39]^a^
Glue Ear: A mother brings her 15-month-old son who has been seen three times in the past year for glue ear. She has heard that this can lead to learning and developmental problems and thinks her child may need surgery. His hearing is normal. Does current evidence support the need for the insertion of tympanostomy tubes to avoid developmental problems in this child? [16]	[40]
Asthma Inhaler: What is the best delivery device for effective administration of inhaled medication to a 5-year-old child during a moderately severe acute asthma attack? [16]	[41]
Nicotine Replacement Therapy after heart attack: A patient staying in hospital had a myocardial infarction two days ago and is now threatening to sign himself out. You suspect this is due to nicotine withdrawal. The patient wishes to stop smoking and seeks your advice on whether he can start nicotine replacement therapy. Is nicotine replacement therapy appropriate for this patient? [16]	[42,43]
Glucosamine sulfate: A 58-year-old woman with long-standing pain of osteoarthritis in knees, hips, and hands asks about the benefits of glucosamine sulfate. Does existing evidence demonstrate that glucosamine has a disease modifying role in osteoarthritis? [16]	[44]

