### Sample Size

The 2 largest and most similar studies [16,18], both commenced with a presearch correct answer rate of around 30% (29% and 32%) and a postsearch rate around 50% (50% and 46%). Using this as our basis, we wanted to be able to discriminate between the postsearch correct answer rate between each of the 3 time-constrained cohorts. Therefore, to derive the sample size, we estimated that the correct answer rates might vary evenly by 10 percentage points between each group, starting at no improvement. This creates 3 datasets with average correct answer rates of 30%, 40%, and 50% for the 3-, 6- and 9-min cohorts, respectively. Applying a 2-proportion statistical comparison (ie, a 2-sample, 2-sided equality) [66], between each pair of answer rates and setting statistical power to 90%, error rate to 5%, and equal sample sizes per cohort, the minimum sample size required is 514 per cohort, which equates to 32 people per cohort sitting 16 tasks or 96 people in total.

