### Task Order, System Rotation, and Task Timing

Task order and system rotation is set as per the table in Multimedia Appendix 4 for each participant to minimize confounding factors. The design is as follows:

A Latin square experimental design is constructed for 16 tasks and 16 participants to minimize the impact of user fatigue on specific tasks.To minimize task order effects, each column of the square is randomized.To incorporate a within-subject design across the system variable, 2 sets of the Latin square derived in (2) are required with alternating use of systems. The first tranche of 16 participants will start their first task with the state-of-the-art system, whereas the second tranche will start with BM25 system. In this way, across the 32 participants, each system will be used equally across all tasks and will experience the same task-order pattern.

The search time allowed for each task is controlled by applying a time limit for each task the participant performs. Participants are randomly assigned to 1 of 3 timing cohorts. The time constraint by task number is specified for each cohort in Multimedia Appendix 5. The rotation of task timing ensures that:

the maximum duration for search in stage 2 is fixed to 96 min for all participantseach task is conducted under all time constraints an equal number of times (32 per cohort)a within-subject design across the time constraint variable such that each participant performs 4 to 6 tasks per time constrainttask time constraints are applied in the same random order according to the task order rotation Latin square, specified above

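### The 1–5 ratings are to be compared by a plain ANOVA although every participant rates tasks under all three time limits and both systems, so the test does not hold its 5% level

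*Protocol article*

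**What the plan says.** **Design.** Under Task Order, System Rotation, and Task Timing, each participant does between four and six tasks at each of the 3-, 6- and 9-min limits. Systems alternate from task to task: "To incorporate a within-subject design across the system variable, 2 sets of the Latin square derived in (2) are required with alternating use of systems". Every task is also done under every limit.

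**Outcomes.** Table 1 collects 1–5 self-ratings for each task: confidence, difficulty, adequacy of time (two items) and stress ("How much stress did you feel due to time pressure").

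**Analysis.** In Statistical Analyses:
- RQ-2, by time limit: "An analysis of variance (ANOVA) will be performed across confidence, difficulty, participant-perceived time impact assessments". The same sentence goes on to search behaviours, which are outside this point.
- RQ-3, by system: "the same ANOVA methods employed for time-constraint categories in RQ-2 analysis will be performed".
- RQ-3, combined: "an ANOVA will be performed across system categories and system time constraints".
- Confounders only: "A covariant analysis (repeated measure ANOVA) will be performed on the task number, task at total duration point (for fatigue), and time transitions".

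No participant or task term is named for the first three.

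**The concern.** Ratings from one person resemble each other, because some people use the high end of a scale and others the low end. A within-subject design lets each rater act as his or her own control, but only if the analysis knows which ratings share a rater. A plain ANOVA treats all 96 × 16 = 1,536 ratings as independent. Differences between raters then stay in the error term, and any variation between raters in how they react to a limit is left out of it. These two errors push the false-positive rate in opposite directions.

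The ratings have a role in RQ2. The section on Time Constraints and Time Pressure treats a limit as pressure only if it is felt as stress, and the stress and time-adequacy items measure that directly. The confidence and difficulty comparisons between limits and systems use the same test.

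**Working it through.** **1. The plan's own figure.** Sample Size gives 514 answers per cohort for 40% v 50% correct, "setting statistical power to 90%, error rate to 5%, and equal sample sizes per cohort". Unpooled formula: (1.960 + 1.2816)² × (0.40×0.60 + 0.50×0.50) / 0.10² = 10.507 × 0.49 / 0.01 = 514.9. The stated 514 reproduces. It concerns the correct answer rate; no power is stated for the ratings. It does fix the number of ratings per limit: 32 × 16 = 512.

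**2. A schedule that fits the design.** Counts at 3/6/9 min of 5/6/5 (15+36+45 = 96 min) or 6/4/6 (18+24+54 = 96 min) meet the fixed 96 min and the four-to-six rule. With one cohort on 6/4/6 and two on 5/6/5, each limit has 16 × 32 = 512 ratings.

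**3. Variance of a limit contrast.** Set total variance to 1. Let ICC be the share due to a constant rater level and τ the share due to rater-by-limit differences.
- Plain ANOVA assumes variance 2/512 for a difference of two limit means.
- The actual variance is about 2[τ/96 + (1 − ICC − τ)/512].
- Ratio of actual to assumed, with 512/96 = 5.33: r = 1 − ICC + 4.33τ.
- For three limits (2 df), the actual false-positive rate at nominal 5% is about 0.05^(1/r).

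**4. Constant rater level only (τ = 0).** Then r = 1 − ICC, which is below 1, so the test is conservative. At ICC 0.3, 0.05^(1/0.7) = 1.4%; at 0.5, 0.05² = 0.25%. Simulation (2,000 runs) gives 1.8% and 0.2%.

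For a single pairwise contrast of 0.15 SD at ICC 0.3, the assumed SE is √(2/512) = 0.0625 and the actual SE is √(0.7×2/512) = 0.0523. Plain test: Φ((0.15 − 1.96×0.0625)/0.0523) = 70%. Participant-blocked test: Φ(0.15/0.0523 − 1.96) = 82%.

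Simulated three-limit F test, 96 people × 16 tasks, schedule of step 2, 3 v 9 min difference 0.15 SD with 6 min halfway:

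| Participant / task ICC (assumed) | False positives, plain | Power, plain | Power, participant and task adjusted |
|---|---|---|---|
| 0.05 / 0 | 4.3% | 55% | 57% |
| 0.2 / 0.1 | 1.8% | 56% | 74% |
| 0.3 / 0.1 | 0.9% | 56% | 79% |
| 0.5 / 0 | 0.4% | 55% | 87% |

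The simulation SE of a power near 55% is √(0.55×0.45/2000), about 1 point. At 0.20 SD, over ICCs from 0.05 to 0.5, power is 83–89% against 85–99%. At 0.25 SD the plain test already has 99% (participant/task ICC 0.3/0.1 and 0.5/0).

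**5. Raters who also respond differently to the limits (ICC 0.3).** Simulated rejection with no true average difference:

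| τ | r | 0.05^(1/r) | Plain ANOVA | Participant intercept only | Repeated-measures ANOVA on means |
|---|---|---|---|---|---|
| 0.05 | 0.917 | 3.8% | 3.6% | 10.2% | 5.3% |
| 0.10 | 1.133 | 7.1% | 8.3% | 17.5% | 5.7% |
| 0.20 | 1.567 | 14.8% | 15.5% | 30.3% | 5.1% |

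Repeat runs put the plain ANOVA at about 8–17% for τ of 0.10–0.20. The direction turns where 4.33τ = ICC, that is at τ = 0.3/4.33 = 0.07 here. A participant intercept alone does worse than the plain test. Repeated-measures ANOVA on each person's mean per limit holds its level.

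**6. Systems.** With 8 ratings per person per system the same algebra gives r = 1 − ICC + 7τ, so the direction turns at a smaller τ. This case was not simulated.

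**The case against.** **The text does not say ordinary ANOVA.** True. A blocked or repeated-measures ANOVA is also an ANOVA, the design section calls the design within-subject, and an article may leave an error term to a fuller document. What weakens this is that the authors do name the repeated-measures form, once, and give it to the confounders rather than to limit or system. The plain reading is an inference, but the better-supported one.

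**The loss may not matter for stress.** This largely stands. A reader might infer that the study is likely to report wrongly that the limits made no difference to stress. The documents do not support that: the Stage 2 section expects pressure in 84%, 50% and 16% of questions at 3, 6 and 9 min, which points to a large contrast, and at 0.25 SD the plain test already has 99% power.

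**Power is not always lost.** This stands. The direction depends on τ, as step 5 shows.

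**Repeated-measures ANOVA would not lose most participants.** A reader might infer that it would, since 96 × 0.95^16 = 42 and 96 × 0.90^16 = 18 people would keep all 16 tasks if 5% or 10% of samples were discarded at random. But a limit comparison needs only one usable rating per limit, and each person has at least four. At 10% random loss the chance of losing all four is 0.1⁴ = 0.0001, so practically all 96 remain. The discard rule is also written for the correct answer rate, and its extension to ratings would be an assumption.

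**Conclusion.** The concern holds in limited form. As worded, the ANOVA for confidence, difficulty, time adequacy and stress does not match the within-subject design and does not hold its nominal 5%. With constant rater differences it is conservative: about 55% power against 74–87% at 0.15 SD and participant ICC 0.2–0.5. The gap is only about 2 points at ICC 0.05 with no task variance, and it largely disappears from 0.25 SD. With rater-by-limit variance of 10–20% of the total (participant ICC 0.3), it rejects about 8–17% of the time under the null.

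The ICCs, τ and effect sizes are assumptions; the protocol gives none of them. The calculations treat a 1–5 rating as a continuous score. The outcomes are secondary, and nothing here bears on the correct answer rate or its tests. The change is worth making because it is nearly free and the result no longer depends on which kind of rater variation is present.

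**What to change.** In Statistical Analyses, replace the ANOVAs of these ratings for RQ-2 and RQ-3 with one linear or ordinal mixed model per rating:
- fixed effects for time limit, system, their interaction and task position;
- crossed random intercepts for participant and task;
- random participant-by-limit and participant-by-system effects, because intercepts alone do not protect the 5% level (step 5);
- limit and system contrasts reported with 95% confidence intervals.

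A simpler acceptable form is a repeated-measures ANOVA on each participant's mean rating per limit, and likewise per system.

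The cost is revised wording, standard software and slightly more analysis work, with no new data and no change to conduct. The one downside is wider intervals if raters respond differently to the limits. In the simulation with ICC 0.3 and τ = 0.10, power at 0.15 SD was 49% for the repeated-measures form against 58% for the plain ANOVA, but the latter figure comes with an 8% false-positive rate.
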